## Abstract

**Background:**

Psoriasis is an inflammatory disease primarily treated through molecular-targeted therapies. However, emerging evidence suggests that dietary interventions may also play a role in managing inflammation associated with this condition. The Mediterranean diet (MedDiet), prevalent in southern European countries, has been widely recognized for its ability to reduce cardiovascular mortality, largely due to its anti-inflammatory properties. This anti-inflammatory potential has prompted interest in exploring the MedDiet’s role in immune-mediated diseases, including psoriasis. Observational studies have indicated potential benefits, such as reductions in the Psoriasis Area and Severity Index. However, there is a need for well-designed clinical trials to address the methodological limitations of these studies and to establish specific dietary recommendations for psoriasis.

**Objective:**

This study aims to evaluate the impact of an intensive dietary intervention based on the MedDiet in patients with psoriasis. The study will assess the effects of this intervention on skin involvement, metabolic parameters, and inflammatory cytokines. In addition, the emotional well-being and quality of life of participants will be evaluated using validated questionnaires. A methodological analysis will also be conducted to enhance the design of future large-scale clinical trials.

**Methods:**

An open-label, single-blinded (evaluator) randomized controlled trial was designed to assess the impact of a high-intensity MedDiet intervention in patients with mild-to-moderate psoriasis. A total of 38 patients will be randomly assigned into 2 groups—an intervention group receiving the MedDiet intervention and a control group receiving standard care. The intervention group will participate in dietary education sessions aimed at adopting the MedDiet over 4 months, with monthly monitoring by experienced nutritionists. Participants will receive 500 mL of extra virgin olive oil per week, along with informative materials, recipes, and weekly menus. In contrast, the control group will receive standard low-fat diet recommendations without nutritionist monitoring. All participants will undergo a baseline visit, a 2-month follow-up visit, and a final visit at 4 months. Blood tests will be conducted at the beginning and end of the study. This study protocol was approved by the Institutional Review Board of the Hospital Ramón y Cajal (Madrid) in July 2023.

**Results:**

Enrollment concluded in October 2024, with data collection set to finish by February 2025. The findings will be presented at national and international conferences and published in peer-reviewed journals.

**Conclusions:**

This protocol outlines the design of a clinical trial that implements the MedDiet in patients with psoriasis to evaluate its benefits on skin involvement, systemic inflammation, and quality of life.

**Trial Registration:**

ClinicalTrials.gov NCT06257641; https://clinicaltrials.gov/study/NCT06257641

**International Registered Report Identifier (IRRID):**

DERR1-10.2196/64277

## Introduction

Psoriasis is a common skin disease, affecting between 2% and 4% of the population [1,2]. Its pathogenesis involves a complex interplay between innate and adaptive immunity, with the interleukin (IL)-17/IL-23 axis playing a crucial role. While not all underlying molecular mechanisms have been fully elucidated, current medical treatments primarily target proinflammatory cytokines [3]. In today’s era of media, nutrition has become a significant topic of interest among patients with psoriasis. A survey conducted by the National Psoriasis Foundation involving 1206 patients revealed that 89% (n=1073) believed it was important to discuss the role of diet in their disease with their physician, and 86% (n=1037) had attempted dietary modifications. Despite this, only 31% (374/1206) of patients had actually discussed dietary changes with a health care provider [4]. In fact, nutritional approaches play a very important role in the prevention and treatment process of chronic diseases such as inflammatory diseases, autoimmune diseases, cardiovascular diseases, and even mental diseases [5,6].

There is well-established evidence supporting the beneficial effect of weight loss in patients with psoriasis [7]. Dietary interventions that promote weight loss are recognized as valuable therapeutic strategies for reducing inflammation, particularly in obese patients with psoriasis [8]. In addition, the nutrigenomic effects of certain food components have been documented [9]. However, the only firm dietary recommendations currently reflected in most psoriasis guidelines and expert consensus are weight loss for patients who are overweight and obese and a gluten-free diet for those with positive celiac disease serology [10]. Therefore, there remains a need for dietary guidance that offers benefits beyond weight loss, applicable to patients of any body weight.

The Mediterranean diet (MedDiet) refers to the eating patterns typical of the olive-growing regions around the Mediterranean Sea. This dietary approach emphasizes the consumption of fruits, whole grains, vegetables, nuts, seeds, legumes, and olive oil—the hallmark of the MedDiet. It also includes a moderate intake of red wine with meals, seafood, poultry, and fermented dairy products, while limiting red and processed meats, sweets, and other ultraprocessed foods [11]. Growing evidence suggests that the MedDiet may influence the progression and severity of psoriasis [12,13]. In a 2018 cross-sectional study by Phan et al [14], which included 35,735 participants from the NutriNet-Santé cohort, 3557 participants had psoriasis, with 878 classified as severe cases. The multivariate analysis, adjusted for factors such as age, sex, weight, and cardiovascular risk, showed a significantly lower percentage of severe psoriasis cases among those with greater adherence to the MedDiet [14].

Several research groups have designed large-scale dietary interventions to implement the MedDiet in large patient cohorts. The PREDIMED (Prevention with Mediterranean Diet) study [15], which included 7447 patients at high risk of cardiovascular disease, randomly assigned participants into 3 groups—2 groups received Mediterranean dietary advice supplemented with extra virgin olive oil (EVOO) or a mixture of nuts, while the third group followed low-fat dietary recommendations. All groups were closely monitored by nutritionists. The PREDIMED study demonstrated the positive role of the MedDiet in preventing cardiovascular events. Subsequent satellite studies, such as the PREDIMAR (Prevention of Recurrent Arrhythmias with Mediterranean Diet) study [16], which used an entirely online dietary intervention, further underscored the MedDiet’s benefits and the feasibility of achieving high adherence to this dietary pattern through a dietary intervention.

The MEDIPSO (Impact of the Mediterranean Diet on Patients with Psoriasis) study, detailed in this paper, was conceived to address the need for more evidence on the relationship between psoriasis and the MedDiet. This proof-of-concept randomized controlled trial, inspired by the PREDIMED study, involves a high-intensity MedDiet intervention in patients with psoriasis. The primary objective is to evaluate the impact of this dietary pattern on psoriasis skin involvement, inflammatory cytokines, and quality of life.

## Methods

### Study Design

The MEDIPSO study is an open-label, single-blinded (evaluator) randomized controlled trial. This experimental study involves patients with mild-to-moderate psoriasis who are on stable topical treatment, which will be randomly assigned to either a control group or an intervention group. Patients in the intervention group will receive dietary education focused on adopting the MedDiet, with monthly monitoring by nutritionists experienced in the PREDIMED clinical trial. In contrast, the control group will not receive any active dietary modification interventions.

Both groups will undergo blood tests to assess metabolic parameters before and after the study period, and data on anthropometric characteristics and quality of life will be collected. The study aims to evaluate the effects of the MedDiet on skin involvement, metabolic parameters, and inflammatory cytokines, as well as its impact on emotional well-being and quality of life. In addition, a methodological analysis will be conducted to refine the design for future large-scale clinical trials.

### Participants

In total, 38 patients with mild-to-moderate plaque psoriasis and no systemic treatment will be included. Participants for this study will be recruited from among patients who regularly attend dermatology consultations at Hospital Universitario Ramón y Cajal. The inclusion criteria and exclusion criteria are stated in Textbox 1.

Inclusion and exclusion criteria for the participation in the Impact of the Mediterranean Diet on Patients with Psoriasis study.
**Inclusion criteria:**
Psoriasis clinically diagnosed by an experienced dermatologistPredominantly psoriasis vulgarisPsoriasis Area and Severity Index ≥2 and ≤10 at the time of recruitmentStable weight (<5% weight loss or gain) in the last 3 monthsTreated exclusively with topical treatment for psoriasis at enrollment and throughout the studyWilling and able to follow the study procedure, attend all scheduled visits during the study period, and provide blood samples as indicated in the procedureAble to give informed consentWilling to implement pregnancy prevention measures throughout the study period
**Exclusion criteria:**
Type 1 or 2 diabetes mellitusGood adherence to the Mediterranean diet at the time of screening (energy-restricted Mediterranean Diet Adherence Screener score ≥8)Language barrier (patients not fluent in Spanish or English) or conditions that make telephone communication difficult (eg, severe hearing loss)History of cardiac diseaseComorbidities that may compromise the implementation of the intervention (eg, cancer, digestive diseases, and so on) or limit survival to less than 6 monthsHistory or current eating disorder (anorexia, bulimia, etc; screening will be carried out using theDiagnostic and Statistical Manual of Mental Disorders, fifth edition, if indicated)Malnourished patients (screening using the Malnutrition Universal Screening Tool, if indicated)BMI greater than 40 kg/m^2^Presenting goutPregnant, planning pregnancy, or breastfeedingUse of diuretics at the time of samplingDifficulty or inconvenience in changing dietary habits and following the Mediterranean diet (allergies, food intolerances, and special diets)Participation in a clinical trial with drugs or dietary intervention in the year prior to inclusion in this study

#### Sample Size

There are no previous studies specifically evaluating the impact of MedDiet on skin involvement in patients with psoriasis. The only dietary intervention study in psoriasis to date is by Castaldo et al [8], which reported a decrease in Psoriasis Area and Severity Index (PASI) of 7.2 (95% CI –8.7 to –5.6) in a sample of 37 patients. However, this study differs significantly from MEDIPSO in design; it involved a single group without a control group, used a highly aggressive intervention including prolonged fasting periods, targeted only patients with obesity who have severe psoriasis, and excluded other adjuvant treatments, with a longer follow-up period.

In contrast, our study includes a control group, applies a less aggressive dietary intervention, and focuses on patients with mild-to-moderate psoriasis who are allowed to continue their stable topical treatments. Consequently, we anticipate the SD in PASI reduction at week 16 to be much lower, around 1. To detect a difference of 1 unit on the PASI scale, with an α risk of 0.05 and a  β risk of less than 0.2 in a bilateral contrast, we estimate that 19 participants per group (intervention and control) are needed. We assume a common SD of 1 and estimate a loss-to-follow-up rate of 15%.

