The molecular mechanisms underlying the potential benefits of the MedDiet on psoriasis severity are not yet well characterized. Beyond psoriasis, greater adherence to the MedDiet has been shown to reduce the severity of other immune-mediated diseases, such as rheumatoid arthritis [24] and inflammatory bowel disease [25]. This observation has shifted attention toward the MedDiet’s potential systemic anti-inflammatory effects. Olive oil, a key component of the MedDiet, is rich in monounsaturated fatty acids. Virgin olive oil, in particular, retains all the lipophilic components of the olive, as well as α-tocopherol and phenolic compounds—molecules with strong antioxidant properties—whereas refined olive oil loses most of its antioxidants during the refining process [26]. Supporting this hypothesis, Mena et al [27] conducted a clinical trial demonstrating that patients who followed a MedDiet supplemented with EVOO exhibited a down-regulation of proinflammatory biomarkers associated with atherogenesis, including serum IL-6, soluble intercellular adhesion molecule-1, and CRP [27].

Our study’s prospective and longitudinal design offers a valuable opportunity to assess how different inflammatory molecules vary following a dietary intervention specifically in psoriasis, potentially illuminating the molecular mechanisms by which the MedDiet exerts its effects in immune-mediated diseases. A key strength and distinguishing factor of this study compared with previous research is the inclusion of a control group, which enhances the ability to attribute observed changes directly to the dietary intervention. This is particularly important given the frequent use of topical treatments in psoriasis patients, regardless of systemic therapy, and the episodic nature of psoriasis, where spontaneous improvements in severity can occur. In addition, maintaining close contact with a small cohort of patients will enable a thorough evaluation of logistical challenges, which will be crucial for planning future larger-scale multicenter trials.

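### The stated beta below 0.2 is narrowly missed under the planned t test even at an SD of 1, and the protocol gives no figure that supports that SD

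*Protocol article*

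**What the plan says.** The primary outcome is the change in PASI from baseline to week 16 (Outcomes). The Sample Size section gives these design inputs:

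- Effect: "To detect a difference of 1 unit on the PASI scale".
- Error rates: "with an α risk of 0.05" and a "β risk of less than 0.2 in a bilateral contrast".
- Spread and loss: "We assume a common SD of 1 and estimate a loss-to-follow-up rate of 15" per cent.
- Result: "we estimate that 19 participants per group (intervention and control) are needed".

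The only numerical evidence on PASI change in that section is one uncontrolled dietary study of 37 patients, with a mean fall of 7.2 and a 95% CI from 5.6 to 8.7. The section lists how that study differs: no control group, a more aggressive diet, obese patients with severe disease, no other adjuvant treatment, and longer follow-up. From these differences it concludes "we anticipate the SD in PASI reduction at week 16 to be much lower, around 1". It reports no pilot estimate, baseline SD, baseline to week-16 correlation or range of SDs.

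Data Analysis names Student's t test for comparing the two groups on variables judged parametric, and the Wilcoxon rank-sum test otherwise.

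**The concern.** In this calculation the SD matters as much as the effect size, because the required number of patients rises with its square. The protocol moves from an SD that can be recovered from its one cited study to a value less than a quarter as large, on qualitative grounds only. One of those grounds, having a control group, concerns how the comparison is made and not how widely patients vary within an arm.

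The section nonetheless presents the power as settled, with beta below 0.2. The trial is also meant to lay the groundwork for a larger study. If the power is taken at face value, a non-significant PASI result could be given more weight against a 1-unit effect than the design can bear, and an SD of 1 could be carried into the next sample size.

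**Working it through.** **Inputs from the Sample Size section.** Difference 1; SD 1 in both arms; two-sided alpha 0.05; power 0.80; loss 15%. Allocation is 1:1 (Randomization).

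**Step 1. Reproduce the plan's figure (normal approximation).**
n per arm = 2 × (1.96 + 0.8416)² × SD² / difference² = 2 × 7.849 = 15.7, so 16.
Allowing for loss: 16 / 0.85 = 18.8, so 19 per arm. The plan's figure is reproduced.

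**Step 2. The same inputs under the t test.**
Evaluable per arm after loss: 19 × 0.85 = 16.15, so 16.
Noncentrality = 1 / (1 × √(2/16)) = 2.83, with 30 degrees of freedom.

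| Evaluable per arm | Power, t test | Power, normal approximation |
|---|---|---|
| 16 | 78.1% | 80.7% |
| 17 | 80.7% | 83.0% |
| 19 (no loss) | 85.1% | 86.9% |

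The t test reaches 80% at 17 evaluable per arm, and 17 / 0.85 = 20 enrolled per arm. With 16 per arm, the largest SD that keeps 80% power is 0.98. With all 19 retained it is 1.07.

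**Step 3. The SD implied by the cited study.**
Half-width of the CI = (8.7 − 5.6) / 2 = 1.55.
SD = 1.55 × √37 / 2.028 = 4.65 using the t quantile, or 1.55 × √37 / 1.96 = 4.81 using the normal quantile.
The planning value of 1 is less than a quarter of either.

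**Step 4. Sensitivity to the SD.** The SDs above 1 are assumptions chosen here to show the slope. They are not in the protocol.

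| SD of change | Power for 1 unit, 16 per arm | Power, 19 per arm (no loss) | Difference detectable with 80% power, 16 per arm |
|---|---|---|---|
| 1.0 (plan) | 78% | 85% | 1.02 |
| 1.25 | 59% | 67% | 1.28 |
| 1.5 | 45% | 52% | 1.54 |
| 2.0 | 28% | 32% | 2.05 |

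Power is by the two-sided t test. The last column is the SD divided by 0.977, the unrounded limit from step 2 for 16 per arm.

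**The case against.** The strongest reply is that 19 per group is correct arithmetic, and that the SD is openly presented as an anticipation. Both are true. By the normal approximation the plan meets its target, and the gap between 80.7% and 78.1% would not matter by itself.

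The reasons for a smaller SD also have substance. Part of the spread in a change score is variation in response, which often shrinks as the response shrinks. In the cited study the SD was 4.65 / 7.2 = 0.65 of the mean. If that ratio held (an assumption), a mean change of 1 to 1.5 would go with an SD of 0.65 to 1.0. Capping PASI at 10 on entry also limits how far scores can fall. So 4.7 is not a sensible planning value here, and these reasons should stay. What they support is a lower SD, not 1 in particular.

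A reader might go further and infer that the eligibility range of PASI 2 to 10 contradicts an SD of 1. It does not. If baseline and week-16 SDs are equal to s, an SD of change of 1 needs a correlation of 1 − 1/(2s²). That is 0.88 at s = 2 and 0.91 at s = 2.31 (uniform entry scores), but only 0.78 at s = 1.5. The protocol gives neither s nor the correlation. The Discussion does mention "the episodic nature of psoriasis, where spontaneous improvements in severity can occur", but as a reason for having a control group, and it does not quantify variance.

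Finally, the limitations paragraph under Expected Findings concedes that the small sample may leave some analyses underpowered, and calls the study proof-of-concept. That softens the point. It does not mention the primary outcome or the SD, so the power stated under Sample Size remains unqualified. Nothing in the protocol proposes reading a null result as absence of effect; that is a risk, not a stated plan.

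**Conclusion.** The point holds in a limited form. On the plan's own inputs, with 16 evaluable per arm and the t test, power is 78%, so a beta below 0.2 is narrowly missed and there is no reserve for a larger SD. The SD of 1 is unsupported by any figure in the protocol, and one of the reasons offered for it is not relevant to it.

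The size of any further shortfall depends on the true SD, which the documents do not give: 59%, 45% and 28% power at assumed SDs of 1.25, 1.5 and 2. These figures assume 15% loss, equal SDs in the two arms and an unadjusted t test. With no loss they would be 67%, 52% and 32%.

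A reader might infer that the sample size was miscalculated, or that the trial cannot detect a 1-unit difference. The documents support neither. The 19 is reproducible, and an SD near 1 remains possible.

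**What to change.** No patients need be added; enrolment ended in October 2024. In the Sample Size section, or in the analysis plan and results paper if the article is fixed:

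1. Replace the single claim of beta below 0.2 with about 78% power for a 1-unit difference (two-sided t test, 16 evaluable per arm) if the SD of change is 1. Add 59% at SD 1.25, 45% at 1.5 and 28% at 2, each labelled as an assumption.
2. Remove the control group as a reason for a low SD. Keep the milder disease and the less aggressive diet as reasons for a value below that of the cited study.
3. State that a non-significant PASI result will be interpreted through the 95% CI for the difference, and not as absence of a 1-unit effect.
4. Report the observed SD of PASI change with its CI, for planning the larger trial.

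The cost is wording only. The downside is that the stated power becomes less favourable.

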#### Randomization

After signing the informed consent, all participants will be enrolled and randomly assigned into either the MedDiet intervention group or the standard-of-care group using closed envelopes. Randomization will be conducted using a computer-generated list created by an independent statistician, who is blinded to the trial and not involved in participant recruitment. The allocation will follow a 1:1 ratio. The recruiter will only open the envelope and learn of each patient’s group assignment after the informed consent form has been signed by the patient.

#### Blinding

The study is single-blinded, as only the investigator evaluating the PASI is blinded. Both the patient, the nutritionists responsible for carrying out the intervention, and the person in charge of follow-up and nonsubjective data collection are aware of the group to which the patient has been assigned.

#### Roles

The entire dermatology department will be involved in patient recruitment. The principal investigator will oversee initial screening, follow-up, data collection, and the evaluation of side effects. Randomization will be conducted using a sealed-envelope system, with the principal investigator opening the envelopes only after the patient has been enrolled in the study and the informed consent has been signed. This investigator will not be blinded.

The nutritional intervention was fully designed by nutritionists from the University of Navarra, who will implement the intervention with the support of the principal investigator. The nutritionists will also not be blinded.

Evaluation of nonobjective parameters, such as PASI, and data analysis will be conducted by coinvestigators who are blinded to the group assignments.

#### The Nutritional Intervention

The objective of the nutritional intervention in the MEDIPSO study is to enhance adherence to the MedDiet. A hybrid approach combining remote and face-to-face interactions will be implemented. During the initial visit, when the first blood sample is taken and the patient’s data are collected, initial dietary recommendations will be provided along with supportive materials, including instructions on the MedDiet, infographics, sample menus, and recipes. Following this, dietitian-nutritionists with experience from previous MedDiet intervention studies, such as PREDIMED, will conduct monthly telephone consultations with each participant.

During these consultations, the dietitian-nutritionists will assess adherence to the MedDiet and set individualized goals for improvement based on the participant’s needs. In addition to the printed materials provided at the first visit, participants will have the opportunity to discuss any questions or concerns with the research team.

Participants in the intervention group will receive 500 mL of EVOO each week, distributed during clinic visits. The goal is to encourage participants to consume at least 4 tablespoons of EVOO daily, using it as the primary culinary fat in their homes as part of the MedDiet.

The dietary recommendations for the intervention will align with the habits defined in the MedDiet according to the Energy-Restricted Mediterranean Diet Adherence Screener (er-MEDAS) scale (Table 1) [17]. Participants will be instructed to follow specific guidelines, including consuming 4 or more tablespoons of EVOO daily for cooking and seasoning; 2 or more servings (200 g per serving) of vegetables per day (with at least 1 serving being raw); 3 or more servings (125 g per serving) of fruits per day (including natural juices); 3 or more servings (60-80 g per serving) of legumes per week; 3 or more servings (150 g per serving) of fish or seafood per week (including at least 1 serving of oily fish); and 3 or more servings (30 g per serving) of nuts per week. Participants will be advised to choose white meats (eg, skinless poultry and rabbit) over red meat (eg, beef and pork) or processed meats (eg, sausages and hamburgers). Regular use of sofrito (a sauce made with chopped tomato, garlic, and onion simmered in olive oil) for cooking, at least twice per week, will also be encouraged. In addition, whole grains (eg, bread, pasta, and rice) should be chosen over refined cereals. The dietary plan will recommend eliminating or limiting the consumption of cream, butter, margarine, carbonated and sugary drinks, baked goods (eg, sweet desserts, cakes, pastries, and cookies), and ultraprocessed foods. The nutritional intervention will not prescribe a specific caloric intake or macronutrient distribution.

**Table 1 table1:** Energy-Restricted Mediterranean Diet Adherence Screener scale score (the maximum possible score is 17; this was the scale used to assess the adherence to the Mediterranean diet during the study; a score ≤7 was considered to be poor adherence to Mediterranean diet).

Question to be asked to the patient	Criterion to score 1 point; otherwise, 0 is recorded
Do you use extra virgin olive oil as the principal source of fat for cooking?	Yes
How many servings of vegetables do you consume per day? Count garnish and side servings as half a serving; a full serving is 200 g.	≥2
How many pieces of fruit (including fresh-squeezed juice) do you consume per day?	≥3
How many servings of red meat, hamburger, or sausages do you consume per week? A full serving is 100-150 g.	≤1
How many servings (12 g) of butter, margarine, or cream do you consume per week?	<1
How many carbonated and sugar-sweetened beverages do you consume per week?	<1
How many servings (150 g) of pulses do you consume per week?	≥3
How many servings of fish and seafood do you consume per week? (100-150 g of fish, 4-5 pieces, or 200 g of seafood)	≥3
How many times do you consume pastry such as cookies, cake, or sweets per week?	<3
How many times do you consume nuts per week? (1 serving=30 g) per week?	≥3
Do you prefer to eat chicken, turkey, or rabbit instead of beef, pork, hamburgers, or sausages?	Yes
How many times a week do you eat cooked vegetables, pasta, rice, or other dishes dressed with sofrito (a tomato, garlic, onion, or leek sauce simmered with olive oil)?	≥2
Do you add sugar to your beverages (coffee, tea)?	No
How many servings of white bread do you consume per day (1 serving=75 g)?	<1
How many servings of whole-grain bread, pasta, or rice do you consume per week?	≥5
How many servings of refined bread, rice, and pasta do you consume per week?	<3
Do you drink wine? How much do you consume per week? (1 cup=100 mL)	Male 14-21 cups; female 7-14 cups

